**Fig. 1 Fig1:**
[figure not shown]
Timeline of assessments from T0 (baseline) to T8, also in relation to the timing of the FMD

**Table 2 Tab2:** Detailed schedule of assessments during follow up

Follow up	Screening	Baseline	In the first month	In the second month	In the fourth month	After six months	In the eighth month	In the tenth month	In the twelfth month	After twelve months
		T0	T1	T2	T3	T4	T5	T6	T7	T8
**Participant characteristics**	X									
**Medical history**	X									
**Anthropometrics**	X	X	X	X	X	X	X	X	X	X
**Blood pressure**	X	X	X	X	X	X	X	X	X	X
**Medication dosage**	X	X				X				X
**Adverse Events**		X				X				X
**Serious Adverse Events**		X	X	X	X	X	X	X	X	X
**MRI**		X				X				X
**Stool sample (including registration form)**		X	X			X				X
**Finger-stick ketone bodies test**		X	X		X		X		X	

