**Questionnaires**										
Cost questionnaire					X	X		X		X
Quality of Life (EQ-5D-5L)		X			X	X		X		X
Treatment satisfaction (DTSQs)		X			X	X		X		X
Treatment satisfaction (DTSQc)										X
Eating habits (DHD-FFQ)		X				X				X
Physical activity (SQUASH)		X				X				X
MRI safety questionnaire	X	X				X				X

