### Outcomes

An overview of the outcomes measured at each stage of the FIT study can be found in Table 2. Height will be measured in cm. Body weight will be measured to the nearest 100 g in light clothing without shoes. Body fat percentage by Bioelectrical Impedance Analysis will be performed in the same conditions. Waist circumference will be measured in cm halfway between the point of the lowest rib and the iliac crest. Blood pressure will be measured with participants seated, an average of two measurements will be taken. For an overview of the different questionnaires used in the FIT study, see Table 2. Participants will be requested to bring a recent overview of their medication use from their GP or their pharmacy.

Finger-stick test for measurement of ketone bodies will be performed in fasting conditions. Blood will be collected in fasting conditions, for details of laboratory tests, see Table 2.

The oral glucose tolerance test (OGTT) will be performed at baseline, after 6 months and after 12 months. Participants will be asked to stop using all glucose lowering medication for 1 day prior to any OGTT. A Venflon catheter will be inserted into an antecubital vein. Participants will be asked to drink a standard solution of 75 g of glucose dissolved in 300 ml of water. Blood will be collected at time 0, 30, 60, 90 and 120 min for measurement of glucose and insulin (at all timepoints).

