### Secondary outcomes

Bodyweight, waist circumference, body mass index and body fat percentage: recorded at baseline and every following study visit.Blood pressure: systolic and diastolic values measured at baseline and every following study visit.Fasting glucose: measured at baseline, after 6 months and after 12 months.Glucose and insulin response to an oral glucose load: OGTT measured at baseline, after 6 months and after 12 months.Plasma lipid profiles: measured at baseline, after 6 months and after 12 months.Metabolomics: measured at baseline and after 12 months.High sensitive CRP: measured at baseline, after 6 months and after 12 months.Dosage of statins and antihypertensive medication: recorded at baseline, after 6 months and after 12 months.Visceral fat, liver/heart ectopic fat, total body fat: from magnetic resonance imaging, measured at baseline, after 6 months and after 12 months.Cardiovascular function: from magnetic resonance imaging, measured at baseline, after 6 months and after 12 months.Gut microbiota architecture: measured from stool samples stored at baseline, after 1 week, after 6 months and after 12 months.Change in dietary pattern: DHD-FFQ measured at baseline, after 6 months and after 12 months [25].Cost-effectiveness analysis: The economic evaluation will consist of both a trial-based cost-effectiveness analysis with a time horizon of 12 months and a model-based cost-utility analysis with a lifetime horizon.Change in physical activity: SQUASH measured at baseline, after 6 months and after 12 months [26].Quality of life: EQ-5D-5L measured at baseline, after 3 months, after 6 months, after 9 months and after 12 months [27, 28].Treatment satisfaction: DTSQs at baseline, after 3 months, after 6 months, after 9 months and after 12 months [29]. DTSQc after 12 months [30].Feasibility in clinical practice: Percentage of fully compliant participants after 12 months, where compliance is based on self-report and laboratory measures. Glucose levels and finger-stick ketone bodies tests are performed after several FMD periods.

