### Baseline data

Baseline data from the two groups will be compared on the following baseline values: age, gender, BMI and metabolic parameters. The values will be summarized using mean and standard deviation, or in case of an asymmetric distribution, by using median and interquartile range.

Hypothesis tests will be carried out using t-tests for independent samples, or, if the assumption of normality is violated, with a Mann-Whitney test. Multiple testing will be corrected for by using the Benjamini-Hochberg procedure. If the groups are found to be imbalanced on one or more covariates, then the following analyses will be adjusted for those covariates. Furthermore, the following analyses will be adjusted for gender and for weight < 100 kg or > 100 kg, since randomization is stratified for these values.

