### Cost-effectiveness analysis

The economic evaluation will consist of both a trial-based cost-effectiveness analysis with a time horizon of 1 year and a model-based cost-utility analysis with a lifetime horizon.

In the trial-based economic evaluation, the effects of the FMD will be compared to usual care and related to the difference in costs. Differences in mean costs and effects (HbA1c -level and QALYs) between strategies will be compared with two-sided bootstrapping. In a net-benefit analysis, costs will be related to the participant reported outcomes and presented in a cost-effectiveness acceptability curve. No discounting will be applied due to the time horizon of the economic evaluation of 1 year. Multiple imputation will be used for handling missing data. The evaluation will be performed from a healthcare and societal perspective. Sensitivity analysis will be carried out for the most important assumptions.

In the model-based cost-utility analysis the UKPDS Outcomes model will be used to estimate lifetime costs and QALYs for the FMD in comparison to usual care [32]. In this lifetime cost-utility analysis costs will be discounted at a percentage of 4% and effects at a percentage of 1.5%, according to the Dutch guidelines for health economic research [33]. Sensitivity analysis will be carried out for the most important input parameters.

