Costs consist of healthcare costs and non-healthcare costs, such as costs of food (cost of the FMD and usual diet) and productivity costs (absence of paid and unpaid work). Healthcare costs concerns the costs of health care use related to diabetes during the year of follow-up e.g. GP visits, visits to dietician, medication. Costs of the FMD will be based on the putative market price. Health care use and absence from work will be assessed with the cost questionnaire (see Table 2). For the valuation of health care, standard prices published in the Dutch costing guidelines will be used [34]. Costs of absenteeism from paid work will be calculated using the friction cost method. Quality-of-life adjusted life-years (QALYs) will be estimated with aid of the EQ-5D-5L. Utilities will be calculated from the EQ-5D-5L questionnaire using the Dutch tariff [35]. Using the area-under-the-curve method for the utility scores obtained for each participant, the QALY outcome per participant will be obtained for the trial-based cost-effectiveness analysis. Furthermore, utility values will be used as input in the model for the lifetime cost-effectiveness analysis.

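### The cost questionnaire is not given at T0, so pre-trial visits and work absence cannot be covariates for the incremental cost: a loss of precision, not a bias

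*Protocol article*

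**What the plan says.** All references are to the protocol article.

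- **Source of the cost data.** The Cost-effectiveness analysis section says: "Health care use and absence from work will be assessed with the cost questionnaire (see Table 2".
- **Timing.** In Table 2 the row "Cost questionnaire" is marked at T3, T4, T6 and T8, and is blank at screening and T0. The quality-of-life row has those four visits plus T0, in line with the Secondary outcomes section: "EQ-5D-5L measured at baseline, after 3 months, after 6 months, after 9 months and after 12 months".
- **Cost window.** "Healthcare costs concerns the costs of health care use related to diabetes during the year of follow-up e.g. GP visits, visits to dietician, medication".
- **Analysis.** "Differences in mean costs and effects (HbA1c -level and QALYs) between strategies will be compared with two-sided bootstrapping". The same section plans multiple imputation for missing data and both a healthcare and a societal perspective. It names no covariate for costs.
- **Baseline data that do exist.** The Table 2 row "Medication dosage" is marked at screening, T0, T4 and T8. The Outcomes section gives its source: "Participants will be requested to bring a recent overview of their medication use from their GP or their pharmacy". HbA1c and EQ-5D-5L are also taken at T0.
- **General adjustment rule.** The Baseline data section says: "If the groups are found to be imbalanced on one or more covariates, then the following analyses will be adjusted for those covariates". It adds adjustment for gender and weight stratum. The values to be compared are age, gender, BMI and metabolic parameters.

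**The concern.** Earlier health care use and absence from work usually predict later use and absence. That makes a baseline cost a natural covariate for the incremental cost, and a natural predictor when missing costs are imputed. Imputation is a practical matter here. The Participant withdrawal section asks people who withdraw to return at T4 and T8, so their T3 and T6 cost questionnaires may well be missing.

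With about 45 people per arm and skewed costs, the arms will differ by chance in prior GP visits, dietician visits and absence. Because these items are not recorded before randomisation, such a difference can be neither described nor used in the analysis. At stake is the width of the interval for the incremental cost and, to a lesser degree, the spread of the net benefit and the acceptability curve. The societal perspective is the more exposed, because it includes productivity costs.

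**Working it through.** **1. Schedule.** Reading Table 2 cell by cell against its header:

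| Row | Visits marked |
|---|---|
| Cost questionnaire | T3, T4, T6, T8 |
| EQ-5D-5L | T0, T3, T4, T6, T8 |
| Medication dosage | Screening, T0, T4, T8 |

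Of the cost components the article names, medication therefore has a baseline value. Visits and work absence do not.

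**2. The plan's own figure.** The article gives no power or precision figure for costs. Its only power statement concerns the binary primary endpoint (5% against 26%, 45 per arm, two-sided 5%, 80% power). It reproduces at 79.6% with a normal approximation, and has no bearing on this point.

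**3. Inputs.** n = 45 per arm (Power calculation section: 100 randomised, 10% loss). The cost SD is not given, so results are in SD units. The correlation r between baseline and follow-up cost is not given either, so 0.3, 0.5 and 0.7 are assumed.

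**4. Size of a chance imbalance.** With equal SDs, the standard error of a between-arm difference is √(2/n) = √(2/45) = 0.211 SD. The 95% range is ±1.96 × 0.211 = ±0.41 SD. This holds for a baseline cost, had it been measured, and for the unadjusted follow-up cost.

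**5. What adjustment would gain.** Linear adjustment for one covariate multiplies the standard error by √(1 − r²). The equivalent unadjusted sample size is 90/(1 − r²). A one-standard-error baseline imbalance shifts the unadjusted incremental cost by r × 0.211 SD.

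| r (assumed) | √(1 − r²) | Adjusted SE (SD) | Reduction in SE | Equivalent total n | Shift from one-SE imbalance (SD) |
|---|---|---|---|---|---|
| 0.3 | 0.954 | 0.201 | 5% | 99 | 0.06 |
| 0.5 | 0.866 | 0.183 | 13% | 120 | 0.11 |
| 0.7 | 0.714 | 0.151 | 29% | 176 | 0.15 |

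The formula is a large-sample approximation. With skewed costs and 45 per arm it is a guide only.

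**6. Where the gain shrinks.** Net benefit also carries the variance of the effect, which a baseline cost does little to reduce. The price of the fasting-mimicking diet falls on one arm and does not depend on earlier health care use, so adjustment has less to offer for that component.

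**7. Who can still be reached.** Follow-up lasts one year (Data collection section) and is expected to finish in June 2021 (Discussion). The last T0 visits therefore fall around June 2020. The article appeared on 24 June 2020, so few participants, if any, remain before T0.

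**The case against.** The strongest case against is that nothing here is wrong or contradictory. Pre-trial cost lies outside the stated window and is not needed to compute a follow-up total, and whether a regression is run inside the bootstrap is a detail that an article may leave to a fuller document. Much of this stands, and it rules out four stronger readings that a reader might infer.

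- *That chance imbalance biases the cost-effectiveness result.* Allocation is randomised in permuted blocks, stratified by gender and weight. The unadjusted comparison is unbiased, and the bootstrap interval and acceptability curve already carry chance imbalance as sampling uncertainty.
- *That the incremental cost cannot be adjusted at all.* Medication dosage, HbA1c and EQ-5D-5L are recorded at T0. The rule in the Baseline data section may already extend gender and weight adjustment to costs. Only prior visits and absence are out of reach.
- *That the T0 reading for EQ-5D-5L shows the cost row to be an oversight.* An area-under-the-curve QALY needs a starting utility. A cost total for the follow-up year needs no starting cost.
- *That a few long absences will dominate the societal result.* Paid absence is valued by the friction cost method, which limits the weight of a long absence.

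It is also true that the size rests wholly on an assumed correlation and is small at its low end. What survives is narrower. Table 2 does fix the timing, so the missing T0 measurement is not a detail left to another document. The precision it forgoes can be partly recovered from data already collected.

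**Conclusion.** The point holds as a minor design weakness in a secondary outcome. Pre-entry visits and work absence are not measured, so they cannot sharpen the incremental cost or help to impute missing costs. The comparison remains valid. The standard error of the incremental cost is larger than it need be by an amount that depends on r: adjustment would reduce it by about 5% at r = 0.3, 13% at 0.5 and 29% at 0.7, with less for net benefit. These figures assume 45 per arm, equal SDs and a linear relation, and no value of r can be taken from the documents. Medication cost alone is likely to sit towards the low end, because entry is limited to lifestyle advice with or without metformin and T0 medication costs may vary little. That last step is a judgement.

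**What to change.** In the Cost-effectiveness analysis section, state that incremental costs are estimated by regression within each bootstrap sample. The prespecified covariates would be gender, weight stratum, T0 medication cost (the T0 medication record priced with the trial's unit costs), T0 EQ-5D-5L and T0 HbA1c. Use the same variables in the multiple imputation model. This needs no new data and one extra analysis step.

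For anyone who has not yet reached T0, add the cost questionnaire at that visit with recall over a stated pre-entry period. For everyone else, report unmeasured baseline resource use as a limitation.

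The cost is one extra questionnaire for the few still to enrol. The downside is that baseline cost would be only partly observed across the trial, and the gain from medication cost alone is likely to be modest.

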### Participant withdrawal

Participants who withdraw from the study will not be replaced. Participants will be asked to return at T4 and T8 for measurements of the primary and secondary endpoints, to be able to perform an intention-to-treat analysis. Subjects can leave the study at any time for any reason if they wish to do so without any consequences. The investigator can decide to withdraw a subject from the study for urgent medical reasons. All data generated up to the time of discontinuation from the study will be analysed and the reason for discontinuation (if known) will be documented.

### Safety

#### Adverse events

Previous experience with this FMD did not reveal serious side effects. Some weakness and headache were sometimes reported. Very few participants dropped out of previous studies because of physical side effects [20, 21]. Hypoglycaemia is not very likely to occur when participants use the FMD while also using metformin, since metformin has no effect on insulin secretion. Metformin will therefore be continued during the FMD. GPs are asked to inform the research team about Serious Adverse Events (SAEs) and Adverse Events (AEs). Participants will be asked at every visit about SAE’s. AE’s will be recorded at several study visits (see Table 2) and during telephone contacts with the research team.

#### Medication use

Medication dosage can be adapted by the GP at any moment according to the Dutch treatment guideline T2D for GP’s [23]. In the event of progression of the diabetes in the FMD group, other medication can be started by the GP in addition to metformin, for example a sulphonylurea derivative. When this occurs during the follow up, sulphonylurea derivatives will be stopped during the FMD, and an additional measurement of fasting glucose 1 week after the FMD will be necessary before the participant can restart this medication. GPs are asked to inform the research team when they start additional glucose lowering medication, so a personal safety plan can be developed for people in the FMD group.

#### Incidental findings

In the informed consent form, participants will give permission to be informed about incidental findings that have important consequences for their health. Their general practitioner will be informed likewise, and will then be asked to start up further diagnostic tests, treatment and/or referral to other specialists. Two examples of incidental findings are an unexpected laboratory result or unknown hypertension. MRI scans are not routinely evaluated by a radiologist for incidental findings. However, incidental findings can occur while performing the MRI scan or during analysis afterwards. Incidental findings that have important consequences for a participants’ health will be reported to the participant and the GP.

#### Monitoring

Monitoring will be done annually according to a monitor plan by internal monitors of the LUMC, since there is a negligible risk a data safety monitoring board will not be formed. A safety report will be submitted to the Medical Research Ethics Committee of the LUMC every year. An interim analysis will not be performed.

## Discussion

T2D can be greatly influenced by lifestyle interventions, including dietary interventions [3]. Improvement in metabolic parameters is certainly possible and may even lead to remission of T2D [6–8]. However, not everyone responds to a dietary intervention in the same way. Furthermore, severe restriction of calories for a longer period of time can be difficult to adhere to. A substantial proportion of people do not adhere to weight loss interventions [10]. Therefore, it is important to have several effective options for management of T2D, so people can find an option in accordance with their preferences. Previous studies have shown that FMDs can be beneficial in mice with hyperglycaemia [36] and healthy subjects [20, 21]. Studies in patients with T2D have not yet been performed.

The advantage of a FMD is that people have major dietary adjustment for a few days every month, and can thereafter return to a more ‘normal’ diet. In the FIT trial, participants do not get dietary advice for the time periods in between the FMD. However, dietary advice for patients with T2D is already part of usual care in general practices [23].

The FIT trial chose to only include T2D patients who are treated with lifestyle advice only or with lifestyle advice and a dose of metformin. T2D patients who use other types of antidiabetic medication, especially insulin, might be at risk for developing hypoglycaemia while using this medication in combination with the FMD. In the FIT trial, GPs and participants are instructed to contact the research team if additional medication is started, to be able to provide a personalised safety plan for the participant. Therefore, if in the FIT trial the use of the FMD improves metabolic parameters and/or reduces the need for medication, additional research is still necessary to assess the safety and effectivity in patients with T2D who use other types of antidiabetic medication.

To conclude, this randomised, controlled, assessor-blinded intervention trial will establish whether monthly cycles of a FMD improve metabolic parameters and/or reduce the need for medication in patients with T2D. In addition, many other health parameters will be measured. Furthermore, a cost-effectiveness evaluation will be performed and the feasibility in clinical practice will be measured as the percentage of compliant patients in the FMD group. Follow up is expected to be completed in June 2021.

## Data Availability

Not applicable for this study protocol. The datasets generated during the FIT trial are at the moment not publicly available due to the ongoing status of the study, but will be available upon completion of the data collection from the corresponding author on reasonable request.

## Abbreviations

AE: Adverse Event
ADF: Alternate Day Fasting
ALAT: Alanine aminotransferase
ASAT: Aspartate aminotransferase
BMI: Body mass index
CRP: C-reactive protein
eCRF: Electronic case report form
FIT: Fasting In diabetes Treatment
FMD: Fasting-mimicking diet
GCP: Good clinical practice
GP: General practitioner
HbA1c: Glycated haemoglobin
HDL: High-density lipoprotein
IGF-1: Insulin-like growth factor 1
IGF-BP-1: Insulin-like growth factor-binding protein 1
LDL: Low-density lipoprotein
LUMC: Leiden University Medical Center
MRI: Magnetic Resonance Imaging
OGTT: Oral glucose tolerance test
SAE: Serious Adverse Event
T2D: Type 2 diabetes
QALY: Quality-of-life adjusted life-years
